**Safety endpoints**

1. Including all adverse events (AEs), serious adverse events (SAEs), study drug-related SAEs, AEs leading to study withdrawal, and AEs related to the study drug occurred during the study period will be recorded.
1. SAEs were defined as death, life-threatening conditions, requiring inpatient hospitalization or prolongation of existing hospitalization.
2. AEs with special concern were defined as drug-related AE listed in the drug information provided by the pharmaceutical manufacture of MMF, including leukopenia or leukocytosis, anemia, sepsis, gastrointestinal symptoms (diarrhea, stomachache, vomiting, anepithymia), certain types of repeated infections (pneumonia, influenza syndrome, urinary tract infection, herpes zoster, etc.), hepatic dysfunction or transaminase elevation, malignancy.

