## 3.7. Safety Endpoints

### 3.7.1. Adverse Events

#### (1) AEs/SAEs

AEs/SAEs occurred during the study period from the first application of MMF to 30±7 days after the last use of MMF will be analyzed and summarized.

**Adverse event (AE):** Any untoward medical occurrence in a patient with the use of a medical product and which does not necessarily have to have a causal relationship (association) with this product. An AE can therefore be any unfavorable and unintended sign (including an abnormal laboratory finding), symptom, or disease temporally associated with the use of the study device, whether or not related to the product.

**Adverse Reaction (AR):** is defined as a response to the study device which is noxious and unintended. An AR is any AE judged as having a reasonable suspected causal relationship to the study device. The assessment of the causal relationship between an AE and the use of the study device is a clinical decision by the investigator based on all available information at the time of the completion of the CRF. The assessment is based on the question whether there was a "reasonable causal relationship" to the study device in question. Possible answers are "yes" or "no".

**Serious adverse event/serious adverse reaction:** an adverse event (AE) or adverse reaction (AR) is serious if it:

- results in death,
- is life-threatening
- requires inpatient hospitalization or prolongation of existing hospitalization.
- results in persistent or significant disability or incapacity
- is a congenital anomaly, birth defect or fetal mental impairment
- is medically significant: Medical and scientific judgment should be exercised in deciding whether an AE/AR may be considered serious (due to an important medical event) because it jeopardizes the health of the patient or may require intervention to prevent another serious condition (death, a life-threatening condition, hospitalization or persistent or significant disability).

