### **6.4. Safety Analysis**

The analysis of safety endpoints will be performed on the SS. For safety analysis, no formal hypothesis testing will be performed. Descriptive analysis will be performed to summarize safety events. Serious adverse events and adverse events will be summarized as the number of events and the number (%) of patients experiencing at least one event. Differences in the proportions of patients experiencing at least one event will be tested using Fisher's exact test.

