#### **6.4.1. Adverse events**

The number, frequency and incidence of the following AEs will be summarized,

1. AEs with special concern include drug-related AEs listed by the pharmaceutical company of the study drug, including leukopenia or leukocytosis, sepsis, gastrointestinal symptoms (diarrhea, stomachache, vomiting, anepithymia), certain types of repeated infections (pneumonia, influenza syndrome, urinary tract infection, herpes zoster, etc.), hepatic dysfunction or transaminase elevation, malignancy.
2. SAEs, study drug-related SAEs, and AEs leading to study withdrawal.

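### The infection item of special concern is limited to undefined 'repeated' infections and no all-infection row is planned, so a single non-serious listed infection may have no infection-specific row

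*Combined protocol and SAP*

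**What the plan says.** SAP 6.4.1 opens with "The number, frequency and incidence of the following AEs will be summarized" and then gives two items. The first begins "AEs with special concern include drug-related AEs listed by the pharmaceutical company of the study drug" and names leukopenia or leukocytosis, sepsis, gastrointestinal symptoms, "certain types of repeated infections (pneumonia, influenza syndrome, urinary tract infection, herpes zoster, etc"), liver abnormalities and malignancy. The second is "SAEs, study drug-related SAEs, and AEs leading to study withdrawal". Neither item is a row for all adverse events or for all infections.

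Protocol 7.7 (Safety endpoints) words the infection item in the same way, so this is not a slip between the two documents. Neither document says how many episodes make an infection *repeated*, over what period, or whether they must be of the same type.

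The general counting rule is in SAP 6.4: adverse events and serious adverse events are summarised as "the number of events and the number (%) of patients experiencing at least one event". Proportions are compared with Fisher's exact test.

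**The concern.** Infections are among the drug-related events that the plan itself singles out for a drug it describes as a potent immunosuppressant. The infection row is where a reader will look for an excess on MMF. If a patient enters it only after a second episode, the row leaves out patients with one listed infection, and small counts could be read as little excess.

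SAP 4.1 adds to this: cells with a count below 10 may be combined, excluded or left as they are, and the study team decides when they are found. A narrower definition makes a sparse infection row more likely.

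**Working it through.** **Which row catches a single infection?**

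| Single listed infection | Row in SAP 6.4.1 |
|---|---|
| Serious (for example one that "requires inpatient hospitalization or prolongation of existing hospitalization") | SAE row |
| Leads to study withdrawal | Withdrawal row |
| Sepsis | Its own special-concern item |
| Non-serious, no withdrawal | No infection-specific row, if *repeated* is taken literally |

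Only the last line is at issue. The *etc.* stands inside the bracket of infection types, so it extends the types and does not lift the word *repeated*.

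**How much could be lost?** The plan states no infection rate or count, so there is no figure to reproduce. Inputs:
- 84 patients per arm (protocol 7.4).
- *Repeated* = two or more episodes per patient (assumption).
- Share p of patients with at least one listed infection = 20% or 40% (assumption).
- Episodes per patient are Poisson, or negative binomial with shape k = 1 or 0.5 to allow for clustering within patients (assumption).

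Formulas, with P(0) = 1 − p:
- Poisson: λ = −ln(1 − p); P(≥2) = 1 − (1 − p)(1 + λ).
- Negative binomial: P(1) = (1 − p) × k × [1 − (1 − p)^(1/k)]; P(≥2) = p − P(1).

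For p = 0.20:
- Poisson: λ = 0.223; P(≥2) = 1 − 0.80 × 1.223 = 0.021.
- k = 1: P(1) = 0.80 × 0.20 = 0.160; P(≥2) = 0.040.
- k = 0.5: P(1) = 0.80 × 0.5 × 0.36 = 0.144; P(≥2) = 0.056.

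| p | Infected, of 84 | P(≥2): Poisson / k = 1 / k = 0.5 | Patients in the row | Share of infected shown |
|---|---|---|---|---|
| 20% | 16.8 | 0.021 / 0.040 / 0.056 | 1.8 / 3.4 / 4.7 | 11% / 20% / 28% |
| 40% | 33.6 | 0.094 / 0.160 / 0.208 | 7.9 / 13.4 / 17.5 | 23% / 40% / 52% |

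**Dependence on the rate.** Take 18 months of MMF plus 30 days (1.58 years) and a Poisson model. Patients with at least one against at least two episodes, of 84, are:
- 0.1 per patient-year: 12.3 against 0.9 (13.0-fold).
- 0.5 per patient-year: 45.9 against 15.8 (2.9-fold).
- 2.0 per patient-year: 80.5 against 69.2 (1.2-fold).

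**Between-arm contrast.** Same window and model, with the rate assumed to double on MMF:

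| Control → MMF rate per patient-year | Risk difference, ≥1 → ≥2 | Risk ratio, ≥1 → ≥2 |
|---|---|---|
| 0.1 → 0.2 | 12.5 → 2.9 points | 1.85 → 3.61 |
| 0.2 → 0.4 | 19.8 → 9.2 points | 1.73 → 3.27 |
| 0.5 → 1.0 | 24.8 → 28.1 points | 1.45 → 2.50 |

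In the first line, expected counts fall from about 23 against 12 patients to 3.4 against 0.9. The power of the planned Fisher test (two-sided 0.05, 84 per arm) falls from 44% to 6%.

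**The case against.** The strongest reply is that the strict reading is not the only one. The named items illustrate a category defined by the manufacturer's list, which is not in these documents. Neither document sets a threshold of two, and the one counting rule the plan does state starts at one event. An analyst could therefore apply that rule to every row and count a single listed infection. That possibility stands. But then *repeated* has no function and should go. If it has a function, the row departs from the rule in SAP 6.4. The wording needs settling either way.

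A reader might also go further than the documents allow:
- *Single infections are not counted at all.* Not so. Protocol 7.7 covers "Including all adverse events (AEs), serious adverse events (SAEs), study drug-related SAEs, AEs leading to study withdrawal", non-serious events are documented too (protocol section 9, Collection), and terms are coded in MedDRA (protocol 7.11). Serious and withdrawal-causing infections have rows. What is missing is an infection-specific row for the remainder.
- *The harm is understated several-fold.* That needs an infection rate that the documents do not give, and the factor ranges from about 13 to 1.2 in the calculation above.
- *The comparison is biased towards no excess.* The restriction applies to both arms. The absolute difference shrinks at low and moderate rates but not at the highest pair shown, and the risk ratio rises in all three.
- *Infection is the main harm of MMF.* The documents list it beside other events without ranking them.

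It is also fair to say that deleting one word does not by itself secure a comparison by arm. Protocol section 9 (Collection) waives adverse-event documentation for patients who have not used MMF. SAP 3.7.1 starts the analysis window at first MMF use, and SAP 5.2 excludes patients who took no study medication. Table 1 nevertheless schedules adverse-event recording at every visit from visit 3, without distinction by arm.

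**Conclusion.** The point holds as a defect in the planned tabulation. The infection item carries an undefined restriction, no all-infection row makes up for it, and it sits poorly with the plan's own at-least-one-event rule. The affected group is patients with a single, non-serious listed infection that does not lead to withdrawal.

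The amount lost is conditional. It rests on reading *repeated* as two or more episodes, on assumed infection frequencies of 20% and 40%, and on the Poisson and negative binomial models. On that basis the row shows between about one tenth and about one half of infected patients, and more where infections are frequent. Because the calculation counts all listed infections, it does not credit the single ones that appear in the SAE or withdrawal rows.

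**What to change.** In SAP 6.4.1 and protocol 7.7, delete *repeated*. Tabulate any infection of the listed types, by type and in total, by arm, as patients with at least one and number of episodes. Recurrent infection can be kept as an additional row, defined as two or more episodes.

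Reconcile protocol section 9 (Collection), SAP 3.7.1 and SAP 5.2 with Table 1, so that control-arm infections are recorded and analysed over a period comparable with the MMF arm. Without this, the by-arm counts remain uncertain however the infection item is worded.

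The wording change costs one word in each document and a few table rows, and uses adverse-event data that Table 1 already schedules. The reconciliation takes more drafting and depends on what was actually recorded for control patients. The downside is that the reported infection figure will look less favourable.

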| Efficacy assessments | 
 
1. Composite outcomes of a doubling of serum creatinine, ESRD, or death due to kidney or cardiovascular cause
 
2. Time to progression of chronic kidney disease
 
3. The time to 30% reduction in eGFR from the baseline.
 
4. Annual absolute changes in the eGFR (eGFR slope) over the trial period.
 
5. Rapid eGFR decline (<math>< -5</math> ml/min/1.73m^2/year).
 
6. Percentage change in the rate of urinary protein excretion at the end of trial over the baseline.
 
                                                                                                                                   |
| Safety assessments   | 
All adverse events (AEs), serious adverse events (SAEs), study drug-related SAEs, AEs leading to study withdrawal, AEs leading to study withdrawal, and AEs related to the study drug
                                                                                                                                                                                                                                                                                                                                                                                                                                                                                                                        |

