#### **Withdrawal or study discontinuation**

In this study, withdrawal from the study is independent of the underlying therapy and will not affect the patient's medical care. Each patient may withdraw from the study at any time and without giving a reason. The investigator also has the right to withdraw participants from the study treatment if they believe that is in the best interests of the participant due to intercurrent illness, SAE, treatment failure, protocol violations, non-compliance, administrative reasons or other reasons. If a patient wants to terminate the study participation, no further data will be collected. In case a patient would like to withdraw the consent given earlier, he/she should inform his/her doctor and the site should document the withdrawal in the (electronic) Case Report Form as well as in the patient medical records.

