**7.10 Trial procedure**

**By visit**

Table 1 lists all of the assessments and indicates with an “X” the visits (data collection) when they are performed. Participants’, who discontinue study drug before completing the study, should be encouraged to attend scheduled study visits for the duration of the follow-up. At a minimum, they will be contacted for safety evaluations during the 30 days following the last dose of study drug, including final contact at the 30-day point. Documentation of attempts to contact the patient will be recorded in the patient record.

All data obtained from the assessments listed in Table 1 must be supported in the patient’s source documentation. Visit dates should be adhered to as closely as possible. If one visit is postponed or brought forward, it should not result in the next visit being postponed or brought forward. The next visit, if at all possible, should adhere to the original time schedule.

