## **Laboratory evaluation**

Laboratory evaluation of all specimens will be performed according to visit procedure.

Renal endpoints that need determined by serum creatinine including doubling in serum creatinine, kidney failure have to be confirmed by two measurements at least 4-weeks apart. For this purpose, patients may need to attend an unscheduled visit one month after the study visit.

Laboratory values that exceed the boundaries of a notable laboratory abnormality should be evaluated by the investigator and additional evaluations should be performed if judged appropriate by the investigator. If the laboratory abnormality is the primary reason for an unforeseen hospitalization or otherwise fulfills the criteria for a Serious Adverse Event, then the procedure for notification of serious adverse events must be followed. Likewise, if the laboratory abnormality leads to discontinuation from the study or from treatment, then the patient must be followed until the abnormality resolves or until it is judged to be permanent.

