### **Collection**

After enrollment into the study, all non-serious adverse events (AE) must be documented on the AE Report Form or in the CRF/EDC system and forwarded to the sponsor within 7 calendar days of awareness. All serious AEs (SAE) must be documented and forwarded immediately (within one business day of awareness). For each AE, the investigator or a delegate must assess and document the seriousness, duration, relationship to product, action taken and outcome of the event.

If a pregnancy occurs during the study, although it is not a serious adverse event itself, it should be documented and forwarded to the sponsor within the same time limits as a serious adverse event. The result of a pregnancy will be followed-up according to applicable SOPs. Any data on abnormal findings concerning either the mother or the baby will be collected as adverse events.

All drug related events must be documented on the product related CRF form or in the CRF / EDC system and also on the PTC form(s). Incidents must be forwarded to the study initiator and funder within 24 hours (immediately) and other events must be forwarded within 7 calendar days of awareness. Products suspected of defects should be retained for recycling and returned to the sponsor for further inspection and verification

The documentation of any AE/SAE/drug related events ends with the completion of the observation period of the patient. However, any AE/SAE - regardless of the relationship and the seriousness - occurring within  $30 \pm 7$  days after the last use of MMF within the study period has to be documented and forwarded to the sponsor within the given timelines, even if this period goes beyond the end of observation.

As long as the patient has not used any MMF within the frame of the study AEs /SAEs do not need to be documented as such in this observational study. However, they are part of the patient's medical history.

For any serious product-related AE occurring after study end, the standard procedures that are in place for spontaneous reporting has to be followed.

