### **4.2. Handling of Lost to Follow Up and Premature Discontinuation**

The distribution of subjects will be presented including the number and percentage of subjects enrolled, screening failure, lost to follow up, discontinuation, and completing the study. For the subjects who failed screening, the number and percentage of subjects for each reason will be clarified and summarized, such as inclusion criteria not met / exclusion criteria met, patient decision, physician decision (medical reason, unable to participate / internal hospital guidelines) and others. The detailed reasons for screening failure of each subject will be presented in the lists.

For the subjects who are lost to follow up or prematurely discontinue the trial, their main reasons will be clarified and summarized, such as patient decision, physician decision, patient voluntary withdrawal, AE, other reasons. The detailed reasons for loss to follow up or premature discontinuation of each subject will be presented in the lists.

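### The only discontinuation measure in the safety plan is AE-driven study withdrawal, so a patient who stops MMF for an AE but stays in follow-up is missing from every planned discontinuation count

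*Combined protocol and SAP*

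**What the plan says.** **What is counted.** SAP 6.4.1 item 2 summarises "SAEs, study drug-related SAEs, and AEs leading to study withdrawal". Protocol 7.7, Safety endpoints, uses the same category: "study drug-related SAEs, AEs leading to study withdrawal, and AEs related to the study drug occurred during the study period will be recorded". The safety row of the protocol abstract prints it twice: "AEs leading to study withdrawal, AEs leading to study withdrawal, and AEs related to the study drug". On disposition, SAP 4.2 states: "For the subjects who are lost to follow up or prematurely discontinue the trial, their main reasons will be clarified and summarized". AE is one of the listed reasons. Neither document plans a count of patients who stopped, interrupted or reduced MMF because of an AE.

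**How stopping the drug is treated.** Protocol 7.8, under withdrawal or study discontinuation, says: "The investigator also has the right to withdraw participants from the study treatment". An SAE is among the reasons given. Protocol 7.10, By visit, says that participants "who discontinue study drug before completing the study, should be encouraged to attend scheduled study visits for the duration of the follow-up". The laboratory part of 7.10 names the two acts separately: "if the laboratory abnormality leads to discontinuation from the study or from treatment".

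**What is recorded.** Protocol section 9, Collection, says that for each AE the investigator or a delegate "must assess and document the seriousness, duration, relationship to product, action taken and outcome of the event".

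**The concern.** Stopping the drug and leaving the study are different events in this protocol, and the safety tables count only the second. For tolerability the first is the relevant one. MMF is planned for at least 18 months (12 months, then a maintenance period of at least 6), so whether patients could stay on it is a main question for any reader of an open-label trial.

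The two rules also pull against each other. The more successfully patients who stop MMF are retained for the intention-to-treat analysis, the fewer of them appear in the withdrawal row. A low count there could mean good tolerability or good retention, and the planned outputs could not tell these apart.

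**Working it through.** The plan states no figure on this point, so there is nothing to reproduce. The check has two parts.

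**1. Following one patient through the plan.** Take a patient who stops MMF at month 3 for leukopenia and attends every visit to week 156.

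- *Withdrawal row (SAP 6.4.1 item 2; protocol 7.7):* the patient has not left the study, so is not counted.
- *Disposition reasons (SAP 4.2):* the patient is neither lost nor an early leaver of the trial, so no reason is summarised.
- *Exposure or compliance:* protocol 7.2 requires tablet counts, but the SAP plans no table of MMF exposure, interruption, dose change or permanent stop.
- *AE and laboratory summaries (SAP 6.4, 6.4.1 item 1, 6.4.2):* the event is counted here. Leukopenia is a named AE of special concern. The AE window in SAP 3.7.1 runs from first MMF use to 30±7 days after last use, so it covers the event that led to stopping.

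The event is therefore visible, but the fact that it ended treatment is not.

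**2. Scale, for illustration.** Inputs:

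- N = 84 per group (protocol 7.4).
- d = share of the MMF arm that stops MMF because of an AE. Not in the documents; assumed 5%, 10% and 20%.
- f = share of those who stay in follow-up. Not in the documents; assumed 50% and 80%, with 100% as the limit.

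Formulas: true AE-driven stops = N × d; shown in the withdrawal row = N × d × (1 − f); missed = N × d × f.

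| d | f | True stops | Shown | Missed |
|---|---|---|---|---|
| 5% | 50% | 84 × 0.05 = 4.2 | 2.1 | 2.1 |
| 5% | 80% | 4.2 | 0.8 | 3.4 |
| 10% | 50% | 84 × 0.10 = 8.4 | 4.2 | 4.2 |
| 10% | 80% | 8.4 | 1.7 | 6.7 |
| 20% | 50% | 84 × 0.20 = 16.8 | 8.4 | 8.4 |
| 20% | 80% | 16.8 | 3.4 | 13.4 |

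At f = 100% the row shows 0 whatever d is. The direction does not depend on the assumed rates. Among patients still taking MMF, leaving the study because of an AE also ends study MMF, so the row cannot exceed the number of AE-driven stops. It falls short as soon as one such patient stays.

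**The case against.** **Only one row is affected.** A reader might infer that MMF will look better tolerated throughout the safety results. The documents do not support that. SAP 6.4 summarises AEs and SAEs by events and by patients, 6.4.1 covers AEs of special concern and drug-related SAEs, and 6.4.2 lists clinically significant laboratory results and summarises values by time point and group. This objection stands, and it limits the point to the discontinuation measure.

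**Study withdrawal is undefined.** Protocol 7.8 places withdrawal from treatment under a heading about withdrawal or study discontinuation, and SAP 4.2 counts discontinuation without qualification before it turns to reasons. A study team could fold drug stops into either. That is possible, but the laboratory text in protocol 7.10 separates the two acts, and the sentence on reasons in SAP 4.2 speaks of discontinuing the trial. If both readings are open, two programmers could produce different counts, which is itself a reason to define the terms.

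**Retention is encouraged, not required.** Protocol 7.10 sets a minimum of safety contact over 30 days after the last dose, so some who stop MMF will leave and be counted. A reader might infer that the row will be close to zero. That holds only if retention is near complete, and the documents give no rate.

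**The repeated item in the abstract.** A reader might take it as a slip for a drug-discontinuation item. Nothing in the documents says so. It shows only that the list needs correcting.

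**Conclusion.** The point holds for the discontinuation measure. Followed as written, the plan leaves a patient who stops MMF for an AE and stays in follow-up out of every discontinuation output, and the error always runs towards too few. Under assumed rates of 5-20% stopping and 50-80% of those staying, about 2 to 13 of 84 MMF patients (2.5% to 16% of the arm) would be missed. Those figures illustrate scale and are not estimates from the documents. No primary or secondary efficacy analysis is affected.

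A reader might also infer that the missing count would explain a diluted intention-to-treat effect. It would help only in part, because patients also stop for reasons other than AEs.

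**What to change.** - Define study withdrawal and MMF discontinuation as separate events in the SAP and the protocol.
- In SAP 6.4.1 item 2 and protocol 7.7, keep the study-withdrawal item and add a descriptive row for the MMF arm: AEs leading to permanent discontinuation of MMF, with number of patients and time from first dose.
- Add interruption and unscheduled dose reduction where the action-taken record shows them, excluding the taper that the protocol already plans. The CRF is not among the documents, so check that its action-taken categories separate these cases.
- Replace the repeated item in the abstract to match.

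Two possible extensions are better left out. Tablet counts and accountability logs give quantities without reasons, so they cannot show that an AE caused a stop. A losartan row for controls would not be comparable: protocol section 9 does not require AE documentation without MMF use, and the window in SAP 3.7.1 starts at first MMF use.

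The cost is some wording and one extra table built on a record that section 9 already requires, with no new visits or procedures. The downside is that reported tolerability may look less favourable.

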#### 7.6 Blind

This is an open-label, blinded end point trial. Both the participant and study personnel will be aware of the treatment assignment. An adjudicating committee, whose members will be unaware of patients' treatment assignments, review the data to determine which patient has reached study end points.

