### **4.4. Multiplicity Adjustment**

For the primary analysis, a two-sided p value of <0.025 was regarded as statistically significant. For the secondary and safety analyses, no multi-test adjustment was employed, and a two-sided p value of <0.05 was regarded as statistically significant. The outcomes are clearly categorized by degree of importance (primary, secondary) and a limited number of subgroup analyses are pre-specified.

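### SAP 6.4 does not exempt study drug-related SAEs from its between-arm Fisher test, although the control count is zero by construction, and the SAP contradicts itself on whether safety is tested at all

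*Combined protocol and SAP*

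**What the plan says.** SAP 6.4.1 names the event groups to be summarised. One item is "SAEs, study drug-related SAEs, and AEs leading to study withdrawal". Another covers events of special concern: "AEs with special concern include drug-related AEs listed by the pharmaceutical company of the study drug", followed by a list of event types.

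The test comes from the parent section, SAP 6.4: "Differences in the proportions of patients experiencing at least one event will be tested using Fisher's exact test". The same paragraph also says: "For safety analysis, no formal hypothesis testing will be performed". SAP 4.4 supplies a threshold: "For the secondary and safety analyses, no multi-test adjustment was employed, and a two-sided p value of <0.05 was regarded as statistically significant". No sentence removes any category from the Fisher comparison.

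Four further facts matter:

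- **Study drug.** MMF is the only one named (protocol 7.2, SAP 3.2). Losartan appears under concomitant medication (protocol 7.3).
- **Control arm.** Controls stay on supportive care, without placebo (protocol 7.9, Visit 6-18).
- **Causality.** Protocol section 9 makes it a yes/no decision by the investigator and asks that the event follow administration of the product. SAP 3.7.1 agrees on who judges: "An AR is any AE judged as having a reasonable suspected causal relationship to the study device" (the word device evidently stands for the study product).
- **Blinding.** Protocol 7.6: "Both the participant and study personnel will be aware of the treatment assignment".

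**The concern.** A between-arm test is informative when both arms could have produced the event under the same definition. A study drug-related SAE does not meet that condition. Unless a control patient receives MMF off-assignment, no investigator can attribute that patient's event to MMF. The control proportion is then fixed at zero by the definition, whatever the control arm's SAE risk.

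What varies is how often investigators who know the assignment answer yes in the MMF arm. A small p-value would be read as evidence that MMF causes serious events, yet it can arise when the two arms have the same SAE risk. The stake is one misleading p-value in the safety tables. The primary and secondary efficacy analyses are not touched.

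**Working it through.** **Inputs.** The documents give no figure for drug-related SAEs. The only figure of theirs used here is the sample size, as a denominator. It reproduces closely (protocol 7.4: 36% against 16%, 80% power, two-sided 0.05). With the pooled two-proportion formula, mean proportion 0.26:

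n = [1.96 × √(2 × 0.26 × 0.74) + 0.8416 × √(0.36 × 0.64 + 0.16 × 0.84)]² / 0.20² = (1.2158 + 0.5083)² / 0.04 = 74.3, so 75 per arm. The protocol states 76. Adding 10%, 76 × 1.10 = 83.6, so 84 as stated.

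I assume a Safety Set of 84 per arm. That is a planning figure; the documents do not give the size of the Safety Set.

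**Step 1: the smallest MMF count that gives p < 0.05.** With x events among 84 MMF patients and 0 among 84 controls, the two-sided Fisher p-value is 2 × C(84, x) / C(168, x).

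- x = 5: 2 × 30,872,016 / 1,050,220,248 = 0.059
- x = 6: 2 × 406,481,544 / 28,530,983,404 = 0.0285

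Six patients with an attributed SAE suffice. At 76 per arm the threshold is the same (0.058 for five, 0.028 for six).

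**Step 2: how often this happens when MMF adds no risk.** Let both arms have the same true SAE risk r, and let a share a of MMF patients with an SAE have it judged related. The attributed incidence in the MMF arm is q = r × a; in controls it is 0. The chance of p < 0.05 is P(X ≥ 6) with X ~ Binomial(84, q). Both r and a are assumed.

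| Attributed incidence q | Example (r × a) | Chance of p < 0.05 |
|---|---|---|
| 2.5% | 10% × 25% | 2% |
| 5% | 10% × 50% | 24% |
| 7.5% | 15% × 50% | 61% |
| 10% | 20% × 50% | 86% |

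The chance passes the nominal 5% at q of about 3.2% and passes 50% at about 6.7%. Below 3.2% the test rejects less often than 5%, but it still does not compare event risks.

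**Step 3: the same test without attribution.** Fisher's test on all SAEs, counted in both arms over a common window, has an exact type I error of 1.7% to 3.4% at 84 per arm for true SAE risks from 5% to 30%. The fault lies in the attributed category, not in Fisher's test.

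**Step 4: dependence on the Safety Set.** SAP 5.2 drops anyone who took no study medication, SAP 3.7.1 ties the AE window to MMF use, and the Collection part of protocol section 9 waives AE recording for patients who have not used MMF. Taken literally, these leave no control denominator and no Fisher test can reject. Steps 1 and 2 describe what happens once that is corrected. The correction does not cure the present point, because the attributed category remains empty in controls.

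**The case against.** **The plan never orders this test by name.** SAP 6.4.1 speaks only of summarising, and SAP 6.4 says safety is descriptive. This stands in part: the test on drug-related SAEs is inferred from a general sentence. But that sentence is in the parent section, exempts nothing, and has a significance threshold in SAP 4.4. An analyst following the SAP could produce the p-value and would find no instruction against it.

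**All SAEs are listed beside the attributed row.** This stands. Once controls are in the Safety Set, an attribution-free comparison is available and the true excess can be estimated. A careful reader may also recognise a study drug-related row as MMF-only. Both limit the harm.

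**The size rests on assumed rates.** This stands too. The results run from 2% to 86%, so the documents support the statement that the test can reject wrongly, not that it will.

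**A stronger reading to avoid.** A reader might infer that events of special concern are also zero by construction in controls, since both documents call them drug-related. The text does not support that. Protocol 7.7 says "AEs with special concern were defined as drug-related AE listed in the drug information provided by the pharmaceutical manufacture of MMF" and then names event types, as does SAP 6.4.1. The adjective explains why a term is on the manufacturer's list; it is not a patient-level causality judgement. A control patient can have pneumonia, herpes zoster or leukopenia and be counted.

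**Conclusion.** The point holds for study drug-related SAEs, and for the AEs related to the study drug that protocol 7.7 lists among its safety endpoints if those are compared between arms. SAP 6.4 and 4.4 disagree on whether safety is tested; if the Fisher sentence is followed, the p-value for attributed events carries no information on whether MMF raises event risk. At an assumed 84 per arm, six attributed cases give p = 0.0285, and false rejection exceeds 5% once about 3.2% of MMF patients have an attributed SAE.

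This assumes that controls have been brought into the Safety Set, that none of them receives MMF, and that the two arms have equal true SAE risk. It does not extend to events of special concern. It is a modest point, worth making because the remedy is nearly free.

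**What to change.** First bring controls into the Safety Set, with AE recording and an analysis window common to both arms; that is a separate correction on which this one depends. Then, in SAP 6.4 and 6.4.1:

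1. State whether safety proportions are tested between arms, and align the two sentences in 6.4 with SAP 4.4.
2. Make the between-arm comparisons on all AEs and all SAEs, regardless of attribution.
3. Report study drug-related SAEs, and the related AEs in protocol 7.7, descriptively for the MMF arm only.
4. State that no between-arm test is made on events selected by a causality judgement.
5. At most, add to the special-concern definition that the listed events are counted in both arms whatever the causality judgement.

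The cost of items 1 to 5 is a few SAP sentences. They need no new data if AEs are recorded in both arms. What is given up is a between-arm p-value for attributed events, which could not be interpreted anyway.
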